### Sample size

No clinical data yet exist on the effect of negative pressure peritoneal therapy on the inflammatory response after damage control laparotomy for intra-abdominal sepsis or injury. Thus, estimates are not available to allow accurate sample size estimation. We therefore propose to undertake a study among a convenience sample of 46 adults. As there are approximately 40 to 50 patients who undergo damage control laparotomy and open abdominal management per year at our institution, this trial should be able to be completed within a 2-year time period.

### Statistical analyses

All continuous variables will be summarized using histograms and measures of central tendency to determine their underlying distribution before statistical descriptions or analyses are conducted. Means (with standard deviations) and medians (with interquartile ranges) will be used to summarize normal and skewed data, respectively. Non-correlated means and medians will be compared using t-tests and Wilcoxon rank sum tests while dependent means and medians will be compared using paired t-tests and Wilcoxon signed rank tests. Differences in proportions will be compared using Fisher’s exact test and risk ratios with associated 95% confidence intervals.

For the analysis of the primary endpoint, we will use a mixed-effects repeated measures linear model to compare the effects of the ABThera™ and Barker’s vacuum pack on changes in plasma IL-6 concentration at 24 and 48 h after TAC dressing application
[75,76]. For longitudinal studies, mixed-effects models have previously been shown to be superior to conventional last-observation-carried-forward approaches for handling missed observations during follow-up
[77,78]. This approach will also be used to compare the plasma concentrations of TNF-α and IL-1, -8, -10, and −12 between groups at 24 and 48 h in the analysis of secondary endpoints.

Multidimensional analysis will be used to assess whether the allocated TAC dressing has an effect on the collective peritoneal and plasma mediator profiles of the study patients. Principal components analysis will be used to reduce the mediator concentration variables into a smaller set of components that account for most of the variability in the data. Component scores will subsequently be calculated along the reduced number dimensions, after which we will attempt to distinguish between patients treated with the ABThera™ and Barker’s vacuum pack using discriminant or latent class analysis. A similar approach will be performed in order to relate inflammatory mediator concentrations to outcomes.

Results will be stratified according to the primary indication for damage control laparotomy (intra-abdominal sepsis or abdominal trauma). While clinical efficacy and safety data will be analyzed according to intention-to-treat methods, mediator data will be examined using per-protocol techniques, with per-protocol treatment being defined as the allocated TAC dressing having been in place for at least 24 h. As the number of conducted statistical tests will be large, we will use the false discovery rate (FDR) procedure developed by Benjamini and Hochberg to restrict the proportion of incorrectly rejected null hypotheses to 0.05
[79-81]. All tests will be two-sided, and only those with an FDR-corrected *P* value (that is q-value) <0.05 will be considered statistically significant
[79]. Stata version 12.0 (Stata Corp., College Station, TX, USA) will be used for all analyses.

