### Patient randomization

To preserve allocation concealment, randomization will be performed using a random treatment generator hosted on a dedicated, publicly available trial website (http://www.peritonealvac.com/). When an eligible patient is identified by the attending surgeon, this website will be accessed by a member of the operating room team and the patient’s last name and hospital number will be entered. The random treatment allocation will then be announced such that the attending surgeon can perform the indicated method of TAC. Variable block size randomization will be performed to ensure equal numbers of patients in each treatment group. Day 1 is considered the day of randomization.

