#### Secondary endpoints and exploration of clinical efficacy and safety

Secondary endpoints of interest include trial feasibility (number of patients enrolled/number of eligible candidates) and the differential effects of the allocated TAC dressings on several physiological and organ dysfunction outcomes, including: (1) the plasma concentration of TNF-α and IL-1, -8, -10, and −12 at 24 and 48 h; (2) the collective peritoneal and systemic mediator profiles (see below); (3) the activation potential of peritoneal fluid
[70,71]; (4) peritoneal fluid drainage volume; (5) postoperative daily fluid balance; (6) SOFA scores and individual organ system components of these scores; (7) the PaO_2_/FIO_2_ ratio; (8) vasopressor requirements and arterial lactate levels; (9) need for renal replacement therapy; (10) RIFLE criteria; (11) APACHE-II scores; and (12) 24 h enteral tolerance (if no gastrointestinal anastomosis was performed).

Secondary clinical efficacy and safety endpoints of interest include: (1) in-hospital death; (2) fascial closure rate and days with fascial closure for the month after admission to hospital; (3) ventilator-free days for the month after admission to hospital; (4) ICU-free days from the month after admission to hospital; (5) hospital-free days from the month after admission to hospital; and (6) risk of renal replacement therapy and days free of renal replacement therapy from the month after admission to hospital. Further, as some have suggested that negative pressure peritoneal therapy may be associated with an increased risk of abdominal fistula formation or development of intra-abdominal hypertension/recurrent abdominal compartment syndrome
[72-74], additional safety outcomes include: (1) intestinal and enteroatmospheric fistula formation; (2) daily IAP; (3) daily WSACS intra-abdominal hypertension grading classification; and (4) risk of abdominal compartment syndrome development.

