Several difficulties were encountered in designing the Intra-peritoneal Vacuum trial. The trial is demanding for study investigators as damage control laparotomy must be performed emergently and is often done at night in our center when research coordinators and laboratory members are unavailable. For these reasons, the randomization interface and enrollment process were simplified in order to prevent delays in application of the TAC device, which could alter patient outcomes. Further, as no objective, evidence-based consensus indications for damage control laparotomy or open abdominal management have yet been described, we were forced to utilize a pragmatic study design, which attempts to mimic actual surgical practice. However, in order to increase understanding, we planned *a priori* to conduct a nested prospective cohort study that will explore indications used for open abdominal management among attending trauma and general surgeons at our center.

As compared to previous translational human studies of physical therapies to reduce peritoneal and systemic inflammation among critically ill adults, this trial will utilize novel laboratory analyses and rigorous statistical techniques. In order to avoid bias with regards to which mediators are measured, we will use the validated Luminex® multiplexing technology to assay a host of pro-inflammatory mediators simultaneously in a cost- and time-efficient manner, maximizing use of the obtained patient samples
[69]. Further, although many authors have conducted comparisons of cytokine concentrations with study endpoints, they frequently ignore the correlation between mediators measured within individual patients over time. Thus, when examining the relationship between cytokines and TAC method, we will use validated statistical techniques that estimate and incorporate this correlation, and which appropriately handle missed observations during follow-up. Finally, in order to collectively analyze the difference in multiple measured mediators between TAC treatment groups, we will also use multidimensional analyses, including principal components analysis.

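### Serial clinical outcomes such as daily fluid balance and intra-abdominal pressure have no stated baseline-adjusted or longitudinal comparison between arms, which costs power and leaves no single estimate per outcome

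*Protocol article*

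**What the plan says.** The Statistical analyses section of the protocol article opens with a rule for all continuous variables. Between independent groups, "Non-correlated means and medians will be compared using t-tests and Wilcoxon rank sum tests"; dependent means and medians get paired t-tests or signed rank tests. The section then assigns a mixed-effects repeated-measures linear model to the primary endpoint, plasma IL-6 at 24 and 48 h. One sentence extends it: "This approach will also be used to compare the plasma concentrations of TNF-α", together with IL-1, -8, -10 and -12. No other outcome is given that model.

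The secondary endpoints section lists postoperative daily fluid balance, "SOFA scores and individual organ system components of these scores", the PaO2/FIO2 ratio, arterial lactate and, among the safety outcomes, daily IAP. The Clinical data section records clinical data until day 28, discharge or death. It gives a measuring frequency only for IAP: every 6 h while the abdomen is open and every 12 h once it is closed.

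On multiplicity, the plan expects many tests and applies the Benjamini-Hochberg procedure to "restrict the proportion of incorrectly rejected null hypotheses to 0.05". Only results with a q-value below 0.05 count as significant.

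**The concern.** Fluid balance and IAP are series within a patient, yet the only method named for comparing them between dressings is an unadjusted test of two independent samples. Such a test handles one value per patient. The article names neither a summary value nor a day for these outcomes, so the analyst may test every day, choose one day, or build a summary. None of these routes, as described, uses a baseline value, and the first two produce no overall treatment effect.

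The article says the trial should supply pilot information for a multicentre trial of clinical outcomes, and it admits that power may be low. In a sample of 46, an inefficient analysis of the organ-function and pressure outcomes weakens what that later trial would build on. If daily tests are run and all enter the false discovery rate list, they also tighten the threshold that each result has to pass.

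**Working it through.** **Inputs from the article.** Sample size: "We therefore propose to undertake a study among a convenience sample of 46 adults". Allocation: "Variable block size randomization will be performed to ensure equal numbers of patients in each treatment group", so about 46 / 2 = 23 per arm. Sidedness: "All tests will be two-sided". The article gives no effect size, SD or power, so there is no figure of its own to reproduce.

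**Assumptions not in the article.** A 0.6 SD effect constant over days; the same correlation rho of 0.3, 0.5 or 0.7 between any two time points, baseline included; m = 3 or 7 post-baseline days; complete data; normal approximation.

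**Step 1, precision.** With outcome SD = 1, power = Phi(0.6 / (sqrt(V) x sqrt(2/23)) - 1.96), where 0.6 / sqrt(2/23) = 2.035.

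- Single day, unadjusted: V = 1, so power = Phi(2.035 - 1.96) = 0.53.
- Mean of m days, unadjusted: V = (1 + (m - 1) rho) / m.
- Mean of m days, baseline-adjusted: V = (1 + (m - 1) rho) / m - rho^2.

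| rho | m | V, mean | Power, mean | V, adjusted mean | Power, adjusted mean |
|---|---|---|---|---|---|
| 0.3 | 3 | 0.533 | 0.80 | 0.443 | 0.86 |
| 0.3 | 7 | 0.400 | 0.90 | 0.310 | 0.96 |
| 0.5 | 3 | 0.667 | 0.70 | 0.417 | 0.88 |
| 0.5 | 7 | 0.571 | 0.77 | 0.321 | 0.95 |
| 0.7 | 3 | 0.800 | 0.62 | 0.310 | 0.96 |
| 0.7 | 7 | 0.743 | 0.66 | 0.253 | 0.98 |

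The range is 0.86 to 0.98 with baseline adjustment and 0.62 to 0.90 with averaging alone. The second range matters because postoperative fluid balance has no evident enrolment value and the article states none for IAP.

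**Step 2, false positives.** In a simulation of 4,000 null trials (23 per arm, 14 outcomes x 7 days = 98 tests), each daily t-test kept an error rate of 0.050 at every correlation tried.

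| rho | Any of 7 days P<0.05, one outcome, unadjusted | Any rejection, Benjamini-Hochberg over 98 tests |
|---|---|---|
| 0.3 | 0.28 | 0.057 |
| 0.5 | 0.24 | 0.053 |
| 0.7 | 0.18 | 0.038 |
| 0.9 | 0.12 | 0.031 |

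The second column does not describe this plan, which requires q<0.05. The third does, if all the daily tests enter the list.

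**Step 3, cost of a longer list.** The strictest Benjamini-Hochberg threshold is 0.05 divided by the number of tests. Take an assumed 0.83 SD effect, for which 23 per arm gives about 80% power at alpha 0.05.

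- One unadjusted test per outcome, 5 to 14 outcomes: thresholds 0.05/5 = 0.010 to 0.05/14 = 0.0036, power 0.59 to 0.46.
- Daily tests, 5 x 3 = 15 to 14 x 7 = 98: thresholds 0.0033 to 0.0005, power 0.45 to 0.25.

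**The case against.** The strongest reply is that the article nowhere says these outcomes will be tested day by day. The t-test sentence is generic, and one value per patient (worst, mean or change) would satisfy it. A condensed article may leave time points and summaries to the full plan. That stands against any claim that daily tests are planned. It does not remove the point, because the article goes far enough to assign the mixed model by name, and the clinical series are outside that assignment.

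Four stronger readings are tempting but unsupported.

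- A reader might infer inflated false positives. Within-patient correlation does not invalidate a between-arm test on a single day, and the q-value rule holds the error (Step 2).
- A reader might infer that every organ-function outcome is measured daily to day 28. Only fluid balance, IAP and the intra-abdominal hypertension grade are called daily; SOFA, PaO2/FIO2 and lactate have no stated schedule; and recording ends at discharge or death.
- A reader might see the Discussion as self-contradictory. Its complaint about other authors is that "they frequently ignore the correlation between mediators measured within individual patients over time". That concerns mediators, and the cytokine analysis answers it. The same reasoning would suit daily IAP, but the article makes no promise there.
- A reader might infer that paired tests will be used to compare dressings. The article does not say so.

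It is also fair that these are secondary, partly exploratory endpoints in a pilot-sized trial that already admits low power. That limits the weight of the point.

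**Conclusion.** The point holds as a worthwhile, inexpensive improvement to secondary outcomes; it is not an error, and the primary analysis is unaffected. Daily fluid balance and daily IAP have no stated longitudinal or baseline-adjusted comparison between arms, and the same applies to SOFA, PaO2/FIO2 and lactate if they are recorded serially. The stated rule permits day-by-day tests without requiring them.

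The loss is one of precision and of a single estimate per outcome. Under the assumptions above, power is about 0.53 for one unadjusted day and 0.86 to 0.98 for a baseline-adjusted average over 3 to 7 days. Where no enrolment value exists, the gain is smaller. It would also shrink if the effect fades over days or if data are incomplete. The further loss from a longer test list arises only if daily tests are run and entered in it.

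**What to change.** In the Statistical analyses section, extend the sentence that carries the mixed-effects model to the secondary cytokines so that it also covers daily fluid balance and daily IAP, and SOFA, PaO2/FIO2 and lactate where they are recorded serially. Specify:

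- the enrolment value as covariate where one exists;
- one early fixed window per outcome, chosen with regard to the section on re-operation and dressing changes, which lets surgeons use any device from the first change, so a long window could dilute a difference between the allocated dressings;
- one average treatment contrast over that window, as the only entry for that outcome in the false discovery rate list;
- daily values as description, with the number alive and measured each day and a note that death and discharge cut the series short.

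Do not extend the linear model to ordinal outcomes (the intra-abdominal hypertension grade and RIFLE) or to binary ones.

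The cost is one or two sentences, since the model is already planned in the same software. The downside is that single-day differences are no longer formally tested.

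### Fisher's exact test for every proportion is valid but conservative at about 23 per arm; Boschloo's test would hold the same 5% limit and recover roughly 0 to 10 points of power

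*Protocol article*

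**What the plan says.** The Statistical analyses section states: "Differences in proportions will be compared using Fisher’s exact test and risk ratios with associated 95% confidence intervals". No other two-arm test for a proportion is named. The rule therefore covers in-hospital death, fascial closure, renal replacement therapy, abdominal compartment syndrome and "intestinal and enteroatmospheric fistula formation", all listed as secondary or safety endpoints.

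The sample is fixed without a power calculation: "We therefore propose to undertake a study among a convenience sample of 46 adults". Allocation aims at balance: "Variable block size randomization will be performed to ensure equal numbers of patients in each treatment group". The analysis is also split by sepsis or trauma: "Results will be stratified according to the primary indication for damage control laparotomy". For these outcomes, "clinical efficacy and safety data will be analyzed according to intention-to-treat methods".

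Significance is decided by a Benjamini-Hochberg q-value below 0.05, not by a raw P value. The procedure is used "to restrict the proportion of incorrectly rejected null hypotheses to 0.05". The limitations paragraph of the Discussion concedes that the trial may be underpowered for clinical and safety endpoints. The article never claims that Fisher's test attains a 5% error rate.

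**The concern.** Fisher's test treats the total number of events as fixed. Randomization fixes the arm sizes but not that total. In small arms, conditioning leaves few possible tables, so the P value moves in large steps and the true error rate falls well short of the nominal level. An unconditional exact test avoids much of this without giving up exact error control. When the sample cannot grow, unused error is unused power, and the endpoints affected include the harms that the article singles out for attention.

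The plan also reports a risk-ratio interval beside the test. The two can point in different directions on the same data.

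**Working it through.** **Inputs.** From the article: 46 patients, equal allocation, two-sided tests, Fisher's test, two strata. Assumed, because the article gives no figure: all event rates, the realised split, and 12 per arm within a stratum. There is no stated power or attained error to reproduce.

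**Method.** With arm sizes n1 and n2, list all (n1+1)(n2+1) tables (x, y). For a rejection region R:

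- rejection probability at (p1, p2) = Σ over R of Bin(x; n1, p1) · Bin(y; n2, p2);
- true size = the maximum of this over a common p1 = p2 = p;
- Boschloo P for a table = the maximum over p of Pr(Fisher P ≤ observed Fisher P).

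Given the event total, Pr(Fisher P ≤ t) is at most t. Averaging over totals keeps it at most t. So the Boschloo P never exceeds the Fisher P on the same table, and Boschloo rejects whenever Fisher does. The enumeration agreed at every split tried.

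**True size at nominal 5%.**

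| Split | Fisher | Boschloo |
|---|---|---|
| 23/23 | 2.60% | 4.75% |
| 22/23 | 3.68% | 4.94% |
| 22/24 | 3.90% | 4.81% |

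**Power (%) at raw 5%, Fisher to Boschloo.** The first rate belongs to the first-named arm. Gains are from unrounded values.

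| Assumed rates | 23/23 | 22/24 | 24/22 |
|---|---|---|---|
| 40 v 15 | 37.3 to 44.2 (+6.9) | 41.7 to 48.6 (+6.9) | 40.4 to 47.0 (+6.6) |
| 50 v 20 | 46.2 to 56.1 (+9.9) | 49.3 to 56.0 (+6.7) | 52.7 to 57.9 (+5.2) |
| 60 v 30 | 43.4 to 53.2 (+9.8) | 47.1 to 48.8 (+1.7) | 51.1 to 51.9 (+0.8) |
| 30 v 20 | 7.3 to 9.8 (+2.5) | 9.1 to 12.2 (+3.0) | 8.4 to 10.9 (+2.5) |
| 20 v 5 | 22.0 to 22.9 (+1.0) | 30.8 to 32.5 (+1.7) | 19.0 to 25.4 (+6.4) |
| 15 v 2 | 17.5 to 17.6 (+0.1) | 29.3 to 29.4 (+0.2) | 10.6 to 20.1 (+9.4) |

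The rare-event rows swing because one table decides them. At 23/23, 5 v 0 gives Fisher P = 2 × 33,649/1,370,754 = 0.0491, which already rejects, so there is little to gain. At 24/22, with the five events in the larger arm, P = (42,504 + 26,334)/1,370,754 = 0.0502, which just misses. More uneven splits can move further: at 25/21 the gain for 25% v 5% is 12.0 points.

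**Strata, 12 per arm, raw 5%.** 40% v 15%: 14.7 to 26.0. 50% v 20%: 21.0 to 32.1. 25% v 5%: 9.0 to 21.0. 30% v 20%: 3.1 to 7.5. The gain is about 4 to 12 points for most pairs, uncommon events included, and 15 for 40% v 10% (23.3 to 38.3). At 11/12 it is smaller: 50% v 20% goes from 27.3 to 32.0.

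**Raw 1%, 23/23.** Size is 0.46% for Fisher and 0.97% for Boschloo. Power for 40% v 15%, 50% v 20% and 60% v 30%: 16.2 to 22.3, 22.4 to 31.8 and 21.2 to 29.4. The gain persists overall. Within strata it shrinks at this cut-off: 50% v 20% goes from 7.3 to 10.8 at 12/12, and the two regions coincide at 11/12.

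**Test against interval.** For 4/23 v 11/23, the risk ratio is 4/11 = 0.364 and SE(log) = √(1/4 − 1/23 + 1/11 − 1/23) = 0.504. The 95% interval is 0.364 · exp(±1.96 × 0.504), that is 0.14 to 0.98. Fisher P = 0.057; Boschloo P = 0.030. The log-scale interval is an assumption, because the article names no method.

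**The case against.** Fisher's test is a standard, valid choice that holds the error below nominal. Whether to condition on the event total is an old disagreement between sound methods. The endpoints are secondary, the article presents itself partly as a pilot, and it already admits low power. Boschloo would still leave about 56% power for 50% v 20% at raw 5%, so no judgement of adequacy changes. The interval example is one chosen table with an interval method that the article does not specify.

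All of this stands, and it limits the point to one of efficiency. Three stronger readings are tempting and are not supported:

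- *The error rate is at most 2.6% at about 23 per arm.* That figure belongs to exact balance. Variable blocks and delayed consent for use of data make an analysed 23/23 uncertain, and one or two patients' imbalance raises the maximum to 3.7% to 3.9%.
- *Death, closure and harms all lose 7 to 10 points.* That range holds for three assumed mid-range pairs at 23/23. For 60% v 30% at 22/24 the gain is 1 to 2 points. For rare harms at 23/23 it is close to nil.
- *The trial misses its 5% level.* Raw 5% is not the decision rule: "All tests will be two-sided, and only those with an FDR-corrected" P value below 0.05 count. The 1% results only illustrate a smaller cut-off; the article fixes none.

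The objection does not reach the comparison itself. An exact test that rejects whenever Fisher does, and sometimes more often, within the same error limit is a better use of 46 patients.

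**Conclusion.** The point holds as a low-severity improvement. Fisher's test gives away part of its permitted error: its maximum size is 2.6% at 23/23 and about 3.7% to 3.9% at 22/23 or 22/24. For the rates tried at these splits, Boschloo's test recovers about 0 to 10 points of power. In strata of 12 per arm it recovers about 4 to 12 points for most pairs. The size figures follow from the arm sizes alone. The power figures depend on event rates and stratum sizes that the article does not give, and they move unevenly with the split. Because Boschloo P values are never larger than Fisher's, Benjamini-Hochberg applied to them rejects at least as much. Nothing in the article is contradictory or invalid on this point, and the primary IL-6 endpoint is untouched.

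**What to change.** In the Statistical analyses section, replace the sentence on proportions with:

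> *Two-arm comparisons of proportions, overall and within each indication stratum, will use Boschloo's unconditional exact test (two-sided). Risk ratios will be reported with 95% confidence intervals from a score or exact unconditional method.*

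This makes disagreement between test and interval rarer, not impossible, so add that the q-value decides significance. Record the change before any comparison of outcomes by arm; the article reports 37 patients enrolled and recruitment continuing.

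The cost is a sentence or two, and possibly a short program or a second package beside Stata 12. No patients, data or procedures change. The caution about low power in the Discussion should stay.

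### For binary endpoints the plan names only a risk ratio, which with about 23 patients per arm will often have no usual interval, or no value, for uncommon harms; a risk difference should be added

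*Protocol article*

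**What the plan says.** The Statistical analyses section of the Protocol article covers all binary endpoints in one sentence, which compares proportions by Fisher's "exact test and risk ratios with associated 95% confidence intervals". Fisher's test supplies a p value and the risk ratio supplies the estimate. No absolute measure is named.

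The section on secondary endpoints lists several binary outcomes. Among the safety outcomes are "intestinal and enteroatmospheric fistula formation" and "risk of abdominal compartment syndrome development", included because some authors have suggested that negative pressure therapy raises these risks. In-hospital death, fascial closure and renal replacement therapy are also listed. No expected rate is given for any of them.

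The Sample size section fixes a "convenience sample of 46 adults". Under Patient randomization, "Variable block size randomization will be performed to ensure equal numbers of patients in each treatment group". The Statistical analyses section adds: "Results will be stratified according to the primary indication for damage control laparotomy", that is, sepsis or trauma. Clinical efficacy and safety data are analysed by intention to treat. The Discussion makes intervention safety one of the things the trial should inform for a later multicenter trial.

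**The concern.** A risk ratio needs events in both arms. With none in the comparator arm, it has no finite value. With none in the ABThera arm, it is zero and has no standard error on the log scale. With none in either arm, it is undefined. In groups of about 23, and smaller ones within each indication, an uncommon harm can easily produce such a table.

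The named measure would then say nothing about the size of any difference, and would give no upper limit for the excess harm compatible with the data. Those two quantities are what a pilot should hand to the designers of the next trial. A p value cannot replace them: Fisher's test can be computed on such a table, but has no estimate beside it.

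**Working it through.** **Inputs.** Total 46 (Sample size) and equal groups (Patient randomization), so 46/2 = 23 per arm. All are counted, because safety is analysed by intention to treat. The 46 is a convenience figure, so the plan has no calculation to reproduce. Event rates are not in the article; 2% to 20%, the same in both arms, is assumed. For the strata, an equal split between sepsis and trauma is assumed, giving 11 or 12 per arm.

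**Step 1: chance of an empty arm.** With m patients per arm and event rate p, P0 = (1 − p)^m, and the chance that at least one arm is empty is 1 − (1 − P0)². For m = 23 and p = 5%: P0 = 0.95^23 = 0.307, and 1 − 0.693² = 0.520.

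| Assumed rate | P0, 23 per arm | At least one arm empty, 23 per arm | Same, 12 per arm | Same, 11 per arm |
|---|---|---|---|---|
| 2% | 0.628 | 86% | 95% | 96% |
| 5% | 0.307 | 52% | 79% | 81% |
| 10% | 0.089 | 17% | 49% | 53% |
| 20% | 0.006 | 1.2% | 13% | 16% |

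Both arms are empty (P0²) in 39%, 9% and 0.8% of trials at 2%, 5% and 10% with 23 per arm. If the rates differ between arms, the chance of at least one empty arm is 37% for 5% against 10%, and 72% for 2% against 6%.

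**Step 2: what the risk ratio gives.** The usual standard error of the log ratio is √(1/x1 − 1/n1 + 1/x2 − 1/n2), which does not exist when x1 or x2 is 0. Adding 0.5 to each cell produces a number, but hardly a useful one.

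**Step 3: what a risk difference gives.** The Newcombe interval combines the Wilson limits (l, u) of the two arms: lower = d − √[(p1 − l1)² + (u2 − p2)²], upper = d + √[(u1 − p1)² + (p2 − l2)²]. For 0/23 the Wilson limits are 0 and 3.8415/(23 + 3.8415) = 0.143. For 2/23 they are 0.024 and 0.268. For 2/23 against 0/23, d = 0.087. The lower limit is 0.087 − √(0.063² + 0.143²) = −0.069 and the upper limit is 0.087 + 0.181 = 0.268.

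| Events (of 23 each) | Risk ratio, log interval | Risk ratio with 0.5 added | Risk difference, Newcombe 95% interval | Fisher p |
|---|---|---|---|---|
| 0 v 0 | none | 1.0 (0.02 to 48.4) | 0 points (−14.3 to +14.3) | 1.00 |
| 2 v 0 | none | 5.0 (0.25 to 98.8) | +8.7 points (−6.9 to +26.8) | 0.49 |
| 5 v 0 | none | 11.0 (0.64 to 188) | +21.7 points (+3.0 to +41.9) | 0.049 |

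The p values are before the planned false discovery rate correction. The last row is an illustration and not a likely result: at a common rate of 5% or 10%, a split of 5 or more against 0 in either direction has a probability of about 0.3% or 1.3%.

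**The case against.** The strongest reply is that this is a condensed article. The interval method, the handling of zero cells and supplementary measures are commonly settled in a full protocol or analysis plan that is not shown, so their absence is no error. That stands, and the point does not rest on a missing zero-cell rule. It rests on what the article does state: one relative measure for every proportion, in a trial of this size.

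Second, the frequency depends on rates that the article does not give. That is also right. At 10% an empty arm is the minority case in the whole trial, nothing in the article shows how uncommon fistula or compartment syndrome is in these patients, and the equal strata are an assumption.

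Third, a reader might infer that the trial would yield no usable safety information. The documents do not support that. Nothing prevents reporting counts per arm, from which a reader can work out exact limits (0/23 has an exact upper 95% limit of 14.8%). Fisher's test remains valid with empty cells. Daily intra-abdominal pressure and the hypertension grade are not binary and are untouched.

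Fourth, the sample size is the main limit on precision. Even the risk difference for 0 against 0 spans about 14 points either way, and the Discussion concedes that power may be low for clinical and safety endpoints. But an imprecise estimate is still an estimate, and that concession does not supply one where the named measure fails.

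**Conclusion.** The point holds as a minor one. For harms at or below about 5%, the ratio or its usual interval fails in half or more of trials with 23 per arm. Between 5% and 10% the share falls from 52% to 17%, and at 20% or more the problem is negligible in the whole trial, though still 13% to 16% within equal strata. What would be missing is the between-group estimate and a bound on excess harm for rare events.

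It would go too far to say that all binary safety and efficacy endpoints are affected. The article gives no rates for death, fascial closure or renal replacement therapy, and if these are at 20% or more, their overall ratios will almost always be estimable. Nor does the arithmetic require the risk ratio to be dropped; preferring an absolute measure throughout would be a matter of taste. The primary IL-6 analysis is not affected. The conclusion rests on assumed event rates, on the usual log-scale interval and, for the strata, on an equal split by indication.

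**What to change.** In the Statistical analyses section, keep Fisher's exact test and the risk ratio, and add one sentence along these lines: for binary endpoints, overall and by indication, we will report events and patients per arm and the risk difference with a Newcombe or Miettinen-Nurminen score 95% confidence interval; risk ratios will be shown where both arms have events.

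This needs no new data, patients or tests. A risk difference carries over less directly to populations with another baseline risk, which is a reason to keep the ratio beside it where it exists. The intervals will remain wide at this sample size, but every table will have one.
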